## Abstract

**Introduction::**

Endoscopic submucosal dissection (ESD) is an advanced therapeutic technique for en bloc resection of superficial gastrointestinal neoplasms. Although gastric ESD is minimally invasive and provides favorable outcomes, it is technically difficult and requires a long procedure time for dissection. The traction-assisted approach overcomes some of the difficulties of gastric ESD, but its ability to reduce the procedure time remains unclear. The traction-assisted approach using dental floss and a clip did not reduce procedure time in the total population, but it reduced procedure time for lesions limited to the greater curvature of the upper or middle of the stomach. Although the traction direction of the clip-with-line method may be limited to the oral side via the cardia, EndoTrac ESD may provide flexible traction at any time during the procedure. This prospective randomized control study has been designed to compare the efficacy and safety of EndoTrac and conventional gastric ESD.

**Methods/design::**

This multicenter, randomized control trial will enroll 150 patients at 2 hospitals in Japan undergoing EndoTrac or conventional ESD for gastric epithelial neoplasia. Patients with a single gastric epithelial neoplasm who meet the inclusion and exclusion criteria will be randomized to EndoTrac or conventional ESD. Patients will be randomized by a computer-generated random sequence with stratification by operator experience, tumor size, tumor location, and institution. The primary endpoint will be ESD procedure time, defined as the time from the start of the submucosal injection to the completion of resection. Other outcomes will include the rates of adverse events and pathological curability

**Discussion::**

The ability of EndoTrac ESD to reduce the long procedure time and/or adverse events observed with conventional ESD can not only reduce physical stress on the patient, but can also reduce length of hospital stay and medical costs. Reduced technical difficulty will contribute to the widespread adoption of this ESD technique worldwide.

**Trial registration::**

University Hospital Medial Information Network Clinical Trials Registry (UMIN-CTR), ID: 000044450; Registered on June 6, 2021.

https://upload.umin.ac.jp/cgi-open-bin/ctr/ctr_view.cgi?recptno=R000050485.

**Protocol version number::**

1.1, March 1, 2022. Patient enrolment began on June 6, 2021 and is expected to be completed by July 19, 2025.

## Introduction

1

Endoscopic submucosal dissection (ESD) is an advanced therapeutic technique for en bloc resection of superficial gastrointestinal neoplasms. This technique is minimally invasive and provides patients with favorable outcomes.^[1–6]^ Although developments in devices and techniques have improved outcomes for patients, gastric ESD is difficult to perform because of its complex technique and the long duration. In particular, maintaining an appropriate view of the correct submucosal layer requiring dissection depends on the location of the lesion. For example, tumors located in the greater curvature of the upper or middle third of the stomach easily sink under water due to gravity, whereas the submucosal layer collapses due to the weight of the tumor itself. Thus, tumor location is an important factor associated with prolonged operation time and difficulty in performing gastric ESD.^[7,8]^

Access to the submucosal layer during gastric ESD may be enhanced by various traction devices.^[9–16]^ Although these devices have contributed to overcoming technical difficulties, the ability of traction to reduce procedure time remains unclear. For example, 1 report comparing conventional ESD with traction-assisted ESD using dental floss and hemoclips suggested that traction devices did not reduce procedure time in the total population, but significantly reduced procedure time for gastric neoplasms located in the greater curvature of the upper or middle third of the stomach, without increasing the rate of adverse events (AEs).^[17]^ Thus, the traction direction of the clip-with-line method for gastric ESD may be limited to the oral side via the cardia. Vertical traction to lesions in the greater curvature of the upper or middle third of the stomach may be able to maintain appropriate traction force to dissect the submucosa.

The EndoTrac traction device (Top Corporation, Tokyo, Japan) is made of a looped nylon thread, a plastic sheath, and a handle (Fig. 1). Pulling the handle pushes the plastic sheath closer to the leading edge of the tumor. The loop is subsequently closed, and the clip is attached to the device. This enables the lesion to be pulled or pushed easily, providing sufficient traction. These findings suggested that the EndoTrac ESD could provide flexible traction at any time during the procedure. To test this hypothesis, a prospective randomized controlled trial (RCT) was designed to test whether EndoTrac traction-assisted ESD provides better procedure-related outcomes than conventional ESD among patients with superficial gastric neoplasms.

**Figure 1 F1:**
[figure not shown]
Photograph of the EndoTrac device. This device is composed of a line with a clinch-knotted loop at a tip that passes through a plastic sheath. There is a T-shaped handle at the end.

## Methods/design

2

### Ethics approval and patient consent

2.1

The study protocol was approved by the Wakayama Medical University Ethics Committee (No. 2958), and conformed to the tenets of the Declaration of Helsinki and Ethical Guidelines for Medical and Health Research involving Human Subjects. The trial has been registered with the University Hospital Medical Information Network (trial registration no. UMIN000044450). Written informed consent will be obtained from all patients enrolled in the study.

### Study aims and design

2.2

This prospective RCT will enroll patients with gastric epithelial neoplasia undergoing ESD at 2 hospitals in Japan. The trial is designed to determine whether EndoTrac ESD provides better efficacy and safety than conventional ESD in patients with gastric epithelial neoplasia. The primary endpoint will be ESD procedure time.

### Patients

2.3

At each center, the on-site study investigators will obtain informed consent from candidates. An electronic data capture system (University Hospital Medial Information Network Internet Data and Information Center for Medical Research Cloud) will be used to input necessary information, confirm that the candidates meet the eligibility criteria (i.e., that the candidates meet all the inclusion criteria and none of the exclusion criteria). The candidates will be registered, and each included candidate will be assigned a registration number. Patients who complete registration will be randomized 1:1 using the minimization method to undergo EndoTrac or conventional ESD using 4 stratification factors: operator experience, tumor size, tumor location, and institution. A flowchart of the study design is shown in Figure 2.

**Figure 2 F2:**
[figure not shown]
Flow chart of the study design. ESD = endoscopic submucosal dissection.

### Inclusion criteria

2.4

Patients will be included if they are aged ≥20 years and have a gastric epithelial tumor eligible for ESD in accordance with the 2020 ESD/endoscopic mucosal resection guidelines for gastric cancer, that is, a clinical diagnosis of intra-mucosal cancer (clinical tumor 1a [cT1a]), indicating a differentiated adenocarcinoma of any size, without ulcerative findings; a class cT1a differentiated adenocarcinoma, ≤30 mm in size, with ulcerative findings, or a class cT1a undifferentiated adenocarcinoma, ≤20 mm in size, without ulcerative findings. These criteria are absolute indications for ESD, whereas other criteria are relative indications.^[18]^ For inclusion, patients will also have to have an Eastern Cooperative Oncology Group Performance status ≤2, and be fully informed about and understand the requirements for study participation, and provide voluntary written informed consent.

### Exclusion criteria

2.5

Patients will be excluded if pre-operative examination shows indications of deep submucosal invasion; the tumor is diagnosed pathologically as not being a gastric epithelial tumor; the tumor cannot be visualized in its entirety; or the tumor crosses the esophagogastric junction or pylorus ring. Patients will also be excluded if they are scheduled to undergo ESD for ≥2 tumors at the same time; have a history of gastrectomy or reconstructive surgery of the gastric tract; have a tendency to bleed (prothrombin time-international normalized ratio >1.5 or platelet count <50,000/μL); are taking 2 or more antiplatelet agents or 1 anticoagulant, with patients taking 1 antiplatelet agent expected to follow appropriate guidelines^[19]^; have serious complications in other organs, defined as an American Society of Anesthesiologists physical status ≥4; are pregnant; or are determined ineligible for any other reason by the principal investigator or sub-investigator.

### Randomization and blinding

2.6

Patients will be randomly assigned 1:1 to undergo conventional ESD or EndoTrac ESD. Random assignment will be centrally controlled by the Internet Data and Information Center for Medical Research cloud version (INDICE Cloud), supported by University Hospital Medial Information Network. Randomization will be performed via dynamic balancing using the minimization method, with stratification by operator experience (trainee or expert), tumor size (≤20 mm or >20 mm), tumor location (upper/middle thirds or lower third of the stomach), and institution. Neither patients nor physicians will be blinded to patient allocation.

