### Primary endpoint

2.8

The primary endpoint will be ESD procedure time, defined as the time from the start of submucosal injection to the end of tumor removal. If an expert replaces a trainee during the procedure, the time required by the expert will be included in the procedure time for the trainee.

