### Secondary endpoints

2.9

Secondary endpoints will include ESD procedure time according to the proficiency of the operator (trainee or expert), tumor size (≤20 mm or >20 mm), tumor location, the presence of an ulcer (UL) (positive or negative), and institution (high volume or low volume center).

Operators who have performed ≤40 ESD procedures previously will be considered trainees, and those who have performed >40 ESD procedures will be considered experts.^[2,7,8,20–22]^ Tumor location will be defined as the affected portion of the stomach (upper, middle, or lower third) or the surface of the stomach (lesser curvature, greater curvature, anterior wall, or posterior wall), according to the Japanese classification of gastric carcinoma.^[23]^ Findings consistent with an UL will be evaluated pathologically, with the presence of an UL or UL scar defined as UL-positive. Institutions performing ≤120 and >120 gastric ESDs per year will be classified as low and high volume centers, respectively.

Also evaluated will be the time for equipping the EndoTrac, defined as the time from insertion of the reusable delivery/development catheter with a hemoclip through the accessory channel of the endoscope to the time when the clip with the EndoTrac is attached to the lesion for traction, and the time from starting traction with the EndoTrac to complete resection. Other secondary outcomes will include the clip slip-off rate during EndoTrac ESD, defined as the number of times a clip slips off the lesion before the end of the procedure; the number of EndoTracs used per patient; and the conversion rate between conventional and EndoTrac ESD.

The rate of damage to the specimen will also be evaluated, and defined in the absence of the EndoTrac as damage within the specimen area delimited by the marked points, or traction-related damage caused by movement of the EndoTrac or the related endoscope within the specimen area delimited by the marked points.

Histologic outcomes will include en bloc, R0, and curative resection rates, tumor depth, sizes of the specimens and tumors, histologic type, ulcerative findings, and margin involvement. En bloc resection will be defined as removal of the entire tumor as a single piece; R0 resection as en bloc resection with lateral and vertical margins free of tumor cells; and curative resection as pathologically eCura A or eCura B, as defined by the Japanese gastric cancer treatment guidelines 2018.^[18]^

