EndoTrac has advantages over clip-with-line traction methods. The EndoTrac can not only control the degree of strength but the direction of traction. Use of the EndoTrac enables coordination of an appropriate direction by pulling or pushing the sheath to achieve the desired traction. The clip-with-line method can pull but not push the lesion, with this 1-way traction resulting in inappropriate or excessive traction, preventing the operator from recognizing the appropriate submucosal layer for dissection.

To the best of our knowledge, the study described herein will be the first prospective randomized control study to compare the efficacy and safety of EndoTrac ESD with that of conventional ESD for gastric tumors. Use of a randomized controlled design can reduce biases associated with retrospective studies, such as patient selection, operator selection, small sample size, and the unconscious choice to use EndoTrac.

Factors associated with technical difficulties and long procedure times for gastric ESD include larger lesion sizes, lesions located in the middle and upper two-thirds of the stomach, lesions located in the greater curvature, presence of ulceration, and an operating physician who has performed <40 of these procedures.^[2,7,8,20–22]^ To determine whether these factors are also associated with greater difficulties in patients undergoing EndoTrac ESD, we plan to randomize patients to undergo EndoTrac or conventional ESD by dynamic balancing using the minimization method, and with stratification by operator experience (trainee vs expert), tumor size (≤20 mm vs >20 mm), tumor location (upper/middle thirds vs lower third), and institution (high vs low volume center). The major limitation of this study is that the operator is not blinded to treatment group allocation.

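### Section 2.6 leaves physicians unblinded without exception, so the pathology endpoints (margins and R0, eCura class, ulcer status) face an avoidable risk of reader bias of unknown size

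*Protocol article*

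**What the plan says.** The only blinding rule is in section 2.6 (Randomization and blinding): "Neither patients nor physicians will be blinded to patient allocation". No exception is made for a pathologist or any other assessor, and no other section provides for masked reading.

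The Discussion (section 5) describes the limitation more narrowly: "The major limitation of this study is that the operator is not blinded to treatment group allocation".

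Section 2.9 (Secondary endpoints) makes three items pathology readings:
- R0: "R0 resection as en bloc resection with lateral and vertical margins free of tumor cells"
- Curability: "curative resection as pathologically eCura A or eCura B"
- Ulcer: "Findings consistent with an UL will be evaluated pathologically"

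Specimen damage, in the same section, has two branches. Without the device it is "defined in the absence of the EndoTrac as damage within the specimen area delimited by the marked points". The other branch is "traction-related damage caused by movement of the EndoTrac or the related endoscope", again within the marked area.

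All of these are secondary. Section 2.8 sets the primary endpoint: "The primary endpoint will be ESD procedure time, defined as the time from the start of submucosal injection to the end of tumor removal".

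**The concern.** An operator cannot be masked to a traction device that he or she is handling. That reason does not extend to whoever later reads margins, curability class and ulcer status on the specimen. Section 2.6 nevertheless gives up blinding for physicians as a group, which is wider than the Discussion justifies.

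Pathological curability is one of the outcomes named in the abstract, and the study aims (section 2.2) and Conclusions promise an answer on efficacy and safety, not on speed alone. Procedure time is measured by people who know the arm. The histology is therefore useful evidence on whether a shorter procedure came at the price of resection quality, and a reader who knows the arm makes that evidence less secure. Ulcer status has a second use: it is one of the factors by which procedure time is broken down (sections 2.9 and 3.2).

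**Working it through.** **1. Who is unblinded.** Section 2.6: patients and physicians, no exception. Section 5: the operator. The two statements differ in scope. Neither names the pathologist, and no section says who reads the specimens or what the request form shows.

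**2. Which endpoints can be read masked.**

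| Endpoint (section 2.9) | Basis | Does the definition need the arm? |
|---|---|---|
| R0, margins | En bloc removal plus tumor-free margins | No |
| Curative resection | Pathological eCura A or B | No |
| Ulcer or ulcer scar | Pathological evaluation | No |
| Specimen damage | Any damage in the marked area without the device; otherwise damage attributed to movement of device or endoscope | Yes |

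Damage therefore drops out. A masked reader could not choose the branch or make the attribution, and the text does not say that damage is judged only on the specimen after the procedure.

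**3. The plan's own figure (section 3.1).** Inputs: 82.2 ± 79.5 and 118.2 ± 71.6 minutes, two-sided 0.05, power 80%, 1:1.
- Difference = 118.2 − 82.2 = 36.0 minutes.
- SD = √[(79.5² + 71.6²)/2] = 75.65 minutes.
- The two-sample t-test needs 70.3, so 71 per arm and 142 in total (the normal approximation gives 70 per arm, 140).
- 142/0.95 = 149.5, so 150.

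The stated 142 and 150 reproduce. They rest on procedure time only, so masking the pathologist does not change them.

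**4. Scale, on assumed rates.** The documents give no R0 rate and no misreading rate. With 150/2 = 75 per arm:
- One reclassified specimen: 1/75 = 1.3 percentage points.
- 95% half-width for a difference, 1.96 × √[2p(1−p)/75]: at p = 0.95, 1.96 × 0.0356 = 7.0 points; at p = 0.90, 1.96 × 0.0490 = 9.6 points.

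Suppose the true rates are equal, at 90% or 95%, and the reader shifts one arm downward. The chance of a significant difference in that direction is then approximately Φ{(shift − 1.96 × pooled SE)/unpooled SE}:

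| Reader shift in one arm | True rate 90% | True rate 95% |
|---|---|---|
| 1 point | 3.9% | 4.5% |
| 3 points | 8.3% | 11.2% |
| 5 points | 15.0% | 21.2% |

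The nominal figure in one direction is 2.5%. These are illustrations, not estimates for this trial.

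**The case against.** The strongest reply is that the point builds on silence. Section 2.6 does not say *all* physicians, the Discussion speaks of the operator only, and the pathologist may never be told the arm. A journal article commonly leaves specimen handling to the full protocol. **This stands in part.** It rules out any claim that the readers are in fact unblinded. It does not remove the point, because the article does state a blinding rule, that rule exempts nobody, and it is wider than the reason given for it.

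Other objections:

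- *Margins and eCura class follow set criteria, and no bias is shown.* This stands. A reader might infer that these endpoints carry a bias; the documents support only a risk. Nor do they say anything about torn or coagulated edges being open to interpretation.
- *Ulceration is a feature of the lesion, and no route is evident by which the arm would sway its reading.* This largely stands. It is the weakest of the three items, but it can be masked under the same arrangement at no further cost.
- *Specimen damage cannot be read masked.* This stands, for the reason shown in the working.
- *Specimens are not the only material open to masked reading.* This stands. Section 2.9 defines perforation partly by imaging and requires imaging evidence for pneumonia, and those images could also be read masked.
- *Only secondary endpoints are involved, with no margin or formal test stated for R0 or curability.* This stands and limits the weight of the point.

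**Conclusion.** The point holds as a matter of design wording and avoidable risk. Section 2.6 and the Discussion disagree on who is unblinded. Taken literally, section 2.6 covers the readers of margins and R0, eCura class and ulcer status, although none of these readings needs the arm. The resulting risk of reader bias is avoidable, and its size is unknown. The figures of 1.3 points per specimen and half-widths of 7.0 and 9.6 points rest on assumed R0 rates of 95% and 90% with 75 analyzed per arm; they show scale only.

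Two stronger readings are not supported. The first is that the pathologists know the allocation and the endpoints are biased: no section says so. The second is that specimen damage belongs with the other three: its definition depends on the device. The primary endpoint and the planned 150 patients are unaffected. This is a cheap improvement to secondary endpoints, not a flaw in the main comparison.

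**What to change.** 1. Reconcile section 2.6 with the Discussion. Suggested wording for 2.6: *open-label for patients and operators; pathologists reading margins, eCura class and ulcer status are masked to allocation.*
2. Send specimens on a request form that carries the registration number and shows neither arm nor device. The same pathologists do the reading.
3. Give specimen damage one arm-neutral definition in section 2.9, for example any damage inside the area bounded by the marking dots, in both arms. Until then, do not place it under masked reading.

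**Cost.** One sentence in 2.6, one in 2.9 and a neutral form; no extra reader and no change to sample size. Masking will be partial, because clip marks may reveal the arm for some specimens. Enrolment began in June 2021, before version 1.1 of March 2022, so specimens read before the change would stay unmasked. The date of the change should be recorded so that the two sets of readings can be told apart.

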### ESD procedures

2.7

Following detection of the lesion, several marking dots will be made outside the lesion, solutions will be injected into the submucosa and circumferential incision and submucosal dissection will be continued to completion. The use of any endoscope, injection needle, hemostatic forceps, or hoods will be permitted, but only a Dual Knife (Olympus) will be allowed for circumferential incision and submucosal dissection. The number of EndoTracs used per patient in the EndoTrac ESD group will be recorded. If a snare technique is required, it can be used without being regarded as a protocol deviation, and this patient will be recorded as undergoing hybrid ESD. Biopsies of other lesions will be allowed before or after ESD on the same day. To ensure the safety of patients during ESD procedures performed by trainees, an expert will be available to continue the procedure when the expert regards the trainee as unable to complete the procedure. If the procedure is time ≥60 minutes, and continuing the assigned procedure is deemed impossible, conversion to the other procedure will be allowed. That is, use of an EndoTrac will be permitted in patients undergoing conventional ESD, and removal of the EndoTrac will be permitted in patients undergoing EndoTrac ESD.

#### Criterion of operator

2.7.1

In this study, the operator must be a research investigator or coordinator who has performed more than 5 ESD procedures for gastric lesions, and at least 1 ESD procedure with an EndoTrac.

